### **7.3. The criteria for early termination of the study:**

- (1) The participant has a disability, life-threatening adverse events, or serious adverse events, and needs to withdraw from the study in advance due to other reasons such as the need for treatment;
- (2) The participant's health condition is at risk for safety and does not allow him to continue to participate in this study;
- (3) Female participants are pregnant (if the vaccination has been completed, the

---

participant does not need to be withdrawn from the study, and follow-up observation is required);

(4) The participant voluntarily requests to withdraw from the clinical study;

(5) The investigator considers the subject unsuitable for further participation in the clinical study.

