|                                                        | 
(9) Diseases affecting the functioning of the immune system (e.g., cancer, except basal cell carcinoma of the skin), congenital or acquired immunodeficiencies (e.g., HIV infection), uncontrolled autoimmune diseases, etc., based on a known medical history or diagnosis;
 
(10) Asplenia or functional asplenia;
 
(11) Long-term use (continuous use for <math>\geq 14</math> days) of immunosuppressants or other immunomodulatory drugs (eg, corticosteroids: prednisone or equivalent; interferon, etc.) within 6 months before study vaccination. Topical medications (e.g., ointments, eye drops, inhalers, or nasal sprays) are permitted and should not exceed the dose recommended in the instructions;
 
(12) Receipt of immunoglobulins and/or blood products within 3 months before study vaccination;
 
(13) Suspected or known alcohol dependence or drug abuse;
 
(14) Participants deemed unsuitable for participation in this study based on the investigator's assessment.
 |
| The criteria for early termination of the study | 
(1) The participant has a disability, life-threatening adverse events, or serious adverse events, and needs to withdraw from the study in advance due to other reasons such as the need for treatment;
 
(2) The participant's health condition is at risk for safety and does not allow him to continue to participate in this study;
 
(3) Female participants are pregnant (if the vaccination has been completed, the participant does not need to be withdrawn from the study, and follow-up observation is required);
 
(4) The participant voluntarily requests to withdraw from the clinical study;
 
(5) The investigator considers the subject unsuitable for further participation in the clinical study.
                                                                                                                                                                                                                                                                                  |

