**Frequency and methods of "visits":**

- From the 7th day after the booster vaccination, remote visits will be conducted at a frequency of twice a week (2-3 days' intervals is recommended), until the 90th day after vaccination: (1) If the number of confirmed primary endpoint cases reaches 162, the frequency of visits will be adjusted to once a month, until the 180th day after vaccination; (2) If the number of confirmed primary endpoint cases does not reach 162, remote visits will still be conducted twice a week. When the number reaches 162, the visit frequency will be adjusted to once a month, until the 180th day after vaccination;
- If the participant has a positive result of SARS-CoV-2 nucleic acid or antigen detection, no matter what stage he/she is in, he/she will be visited twice a week (2-3 days' interval is recommended), until his/her nucleic acid or antigen detection result turns negative or the symptoms disappear or stabilize under the investigator's assessment;
- Remote follow-up methods include text messages, phone calls, videos, photos, etc. On-site visits are carried out according to the above monitoring process and actual conditions.

---

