### **➤ Long-term safety observation**

All serious adverse events (SAEs), adverse events of special interest (AESIs), and pregnancy-related events within 6 months after vaccination will be collected from all participants.

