#### **7.4. Participant withdrawal from the study:**

Participant withdrawal from the study: the participant cannot continue to complete the visits specified in the protocol due to reasons such as meeting the criteria for early termination of the study or being unable to be contacted. Including but not limited to:

(1) The participant could not complete the follow-up visit because they met the 7.3 criteria for early termination;

(2) The participant could not be contacted within the visit time scheduled in the study protocol, and it is confirmed that the subject cannot attend all subsequent visits;

(3) The participant permanently left the original place of residence and lost contact.

The investigator should inform the participant of the right to withdraw from the study at any time. The withdrawn participants will not be replaced, and the investigator should try to contact the participants who failed to return to follow-up at the scheduled time. All data collected before withdrawal could be used for analysis. When a participant withdraws before study completion, the date and reason for withdrawal is to be documented in the eCRF and the source document, with a detailed description of the situation:

(1) Serious adverse events

(2) Adverse events (but not serious adverse events)

(3) Protocol violations

(4) Voluntary withdrawal, but not due to adverse events

(5) Going out, migrating, or moving away from the study site

(6) Loss to follow-up

---

(7) Death

(8) Other

A clear distinction must be made between subjects who withdraw from the study due to an adverse event and those who withdraw for other reasons. After withdrawal or termination of the study for the participants who have received the study vaccine, the investigator shall provide necessary treatment for the study-related clinical conditions of the participants, and follow up on the adverse events/serious adverse events until the definite diagnosis/stable disease/recovery.

Definition of withdrawal time: the time when the investigator decides to terminate the participant from the study or the time when the participant voluntarily withdraws from the study.

Definition of completion of clinical study: The clinical study is considered to be completed within 6 months after the subject completes the protective efficacy and safety visit after the booster immunization.

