## **9.3. Route of Vaccination and Immunization Procedure**

Site and route of administration: The site of administration is the lateral deltoid muscle of the upper arm, and the route of administration is intramuscular injection.

Immunization procedure: The participant assigned to the study vaccine group received 1 dose of the study vaccine on Day 0. The participants assigned to the placebo group received 1 dose of placebo on day 0.

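### After the only dose, Sections 7.3(1), (2) and (5) and 7.4 do not separate ending participation from ending observation, and they conflict with the 6-month collection in Section 6.7

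*Protocol*

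**What the plan says.** Protocol Section 9.3: a participant in the study vaccine group "received 1 dose of the study vaccine on Day 0". The placebo group likewise receives one injection on Day 0, and no later dose is planned.

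Protocol Section 7.3 (repeated in the Synopsis) lists five criteria for early termination. Criterion (1) applies when "The participant has a disability, life-threatening adverse events, or serious adverse events, and needs to withdraw from the study in advance", with the need for treatment as the example reason. Criterion (2) is a health condition that puts safety at risk and does not allow the participant to continue. Criterion (3) is pregnancy, with an exception: "if the vaccination has been completed, the participant does not need to be withdrawn from the study, and follow-up observation is required". Criterion (4) is the participant's own request. Criterion (5) is the investigator's view that the participant is unsuitable.

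Protocol Section 7.4 treats a participant who meets a 7.3 criterion as not completing the follow-up visits. It allows the investigator's decision to set the withdrawal time and names data collected before withdrawal as usable. After withdrawal, the investigator must treat study-related conditions and "follow up on the adverse events/serious adverse events until the definite diagnosis/stable disease/recovery". A footnote to the schedule of activities (Table 1) adds one end-of-study call if the participant decides to stop early.

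Protocol Section 6.7 says that SAEs, AESIs and pregnancy-related events "within 6 months after vaccination will be collected from all participants". Section 6.6 sets COVID-19 surveillance to Day 180, mainly by remote contact: "Remote follow-up methods include text messages, phone calls, videos, photos, etc".

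**The concern.** In a multi-dose trial, a termination rule for safety has a purpose: it stops further exposure. Here there is nothing left to stop once the participant has been dosed, so criteria (1), (2) and (5) can act only on data collection. All three depend on the participant's health or conduct after the dose, and health after an mRNA vaccine can differ from health after saline. Participants removed on these grounds are therefore not a random sample of either arm.

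Two kinds of data are at stake. One is new SAEs and AESIs between termination and month 6, which feed the secondary safety endpoints. The other is symptomatic, severe and fatal COVID-19 arising after termination, which feeds the primary and secondary efficacy endpoints. If sicker participants leave observation more often in one arm, the comparison of those endpoints can be distorted, and no analysis can recover events that were never collected. Section 11.8.4 says that missing safety data will not be processed.

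**Working it through.** **Setting the passages side by side**

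1. *What termination can do.* One dose on Day 0 (Section 9.3) means that, for a dosed participant, termination ends observation only.
2. *Which criteria keep a dosed participant under observation.* Only (3), pregnancy, says so. Criterion (4) is the participant's choice and must end contact if consent to contact is withdrawn. Criteria (1), (2) and (5) are silent.
3. *What continues after termination.* Section 7.4 follows AEs and SAEs to diagnosis, stability or recovery. Section 12.4 follows vaccination-related events that persist after termination to their end. Section 12.5.1 follows reported SAEs to recovery or stability. Section 8.3 follows pregnancies in the collection period. The end-of-study call is a single contact, worded for a participant who chooses to leave. None of these provides for COVID-19 case surveillance, or for finding new SAEs and AESIs, up to month 6.
4. *What Section 6.7 requires.* Six months of SAE, AESI and pregnancy collection from all participants. Points 3 and 4 do not fit together.
5. *Whether the grounds make observation impossible.* In general they do not. Section 10 places no restriction on drugs needed to treat an adverse event, so a need for treatment does not in itself conflict with staying under observation. Routine surveillance is remote, and Sections 11.2.5 and 11.2.6 limit Visits 5 and 6 to the immunogenicity subgroup (100 of 3,200). A swab is needed only when symptoms appear.
6. *Effect on the analysis sets.* Under Section 11.8.1, E-mFAS needs one surveillance contact at 14 days after vaccination. Someone terminated before that contact drops out of the primary analysis set. Someone terminated later stays in it with shortened observation.

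**Is this a power problem?**

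Inputs from Section 6.5.1: control incidence 9%, VE 60%, margin 30%, 1:1 allocation, one-sided alpha 0.025, power 90%, exact conditional method.

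- Expected cases per pair of participants (one in each arm): 0.09 + 0.09 × 0.4 = 0.126.
- Plan's figure: 162 / 0.126 = 1,285.7, so 1,286 per group is reproduced. The exact conditional test at 162 cases succeeds with 54 or fewer vaccine cases and has power 92.2%, so 162 is adequate.
- Allowance: 1,286 / 0.8 = 1,607.5, close to the 1,600 planned.
- With no loss: 1,600 × 0.126 = 201.6 cases.

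Power averaged over a Poisson total, by overall loss from 1,600 per group:

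- 10% loss: 181.4 cases, power 93.7%
- 20% loss: 161.3 cases, power 90.6%
- 25% loss: 151.2 cases, power 88.6%
- 30% loss: 141.1 cases, power 86.1%

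Losses within the planned 20% keep the stated power. What remains is selection, which a sample-size allowance does not address.

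**The case against.** The strongest reply is that the protocol protects most of what matters. Data before withdrawal are kept, and existing events are followed. The SAE that triggers a termination has already been recorded, so it is not missing from SAE incidence. Section 6.6 also keeps test-positive participants on twice-weekly visits, whatever stage they are in, until the test turns negative or symptoms resolve or stabilise. And the wording in Section 6.7 could be read as a collection schedule, not a promise that overrides withdrawal. All of this stands and limits the point to events that are new after termination. It does not close the gap: no passage says that surveillance or new-event collection survives termination under (1), (2) or (5), while (3) says it for pregnancy.

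A reader might infer more than the documents support:

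- *That any SAE ends follow-up.* Criterion (1) also requires that the participant "and needs to withdraw from the study in advance due to other reasons such as the need for treatment". An SAE alone is not enough.
- *That protocol violations or moving away end follow-up.* Items such as "Going out, migrating, or moving away from the study site" stand in a list of reasons to be recorded when a withdrawal has occurred. They are not criteria in Section 7.3. The rule on moving, 7.4(3), requires a permanent move and lost contact together.
- *That deaths from COVID-19 would be missed once the case is diagnosed.* Section 6.6 continues visits to positive cases and has case outcomes recorded, and Section 7.4 need not mean that diagnosis alone ends follow-up. The documents do not settle the point for a terminated participant, so this scenario is speculative.
- *That criterion (1) should simply be limited to participants not yet vaccinated.* Adverse events are defined as occurring after vaccination (Section 12.1), so that would empty the criterion.

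**Conclusion.** The point holds in a limited form. As written, Sections 7.3(1), (2) and (5) with 7.4 allow a dosed participant to leave observation for reasons tied to post-dose health. COVID-19 outcomes and new SAEs or AESIs to month 6 may then be lost, contrary to Section 6.7. They may be lost; the documents do not show that they are.

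The size and direction of any bias cannot be computed, because the protocol gives no expected number of withdrawals by reason or arm; the 20% is an overall non-evaluable allowance. Power is not threatened within that allowance, assuming 9% control incidence and 60% VE. That the loss is informative is an inference from the nature of the grounds, not a figure in the plan. This concerns what is collected, so an analysis plan could not repair it. It is an inexpensive improvement and does not invalidate the design.

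**What to change.** Reconcile Sections 7.3 and 7.4 (and the Synopsis) with Section 6.7 by extending the clause in 7.3(3) to criteria (1), (2) and (5):

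- After vaccination, these criteria do not by themselves end observation.
- Participants who still consent to contact stay in remote COVID-19, SAE, AESI and pregnancy follow-up to Day 180, with swabs as already planned.
- Data collected after the triggering event are used in the analysis.

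Leave criterion (4), voluntary withdrawal, in place. Keep the reason codes in Section 7.4 for documentation, with a note that moving ends follow-up only when contact is also lost, as 7.4(3) states.

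The cost is a wording change in the protocol and the eCRF withdrawal form, plus a few more contacts, and swabs where needed, with participants who are ill. The contacts and swabs use procedures already in Section 6.6. No treatment or clinical rule changes.

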#### **7.4. Participant withdrawal from the study:**

Participant withdrawal from the study: the participant cannot continue to complete the visits specified in the protocol due to reasons such as meeting the criteria for early termination of the study or being unable to be contacted. Including but not limited to:

(1) The participant could not complete the follow-up visit because they met the 7.3 criteria for early termination;

(2) The participant could not be contacted within the visit time scheduled in the study protocol, and it is confirmed that the subject cannot attend all subsequent visits;

(3) The participant permanently left the original place of residence and lost contact.

The investigator should inform the participant of the right to withdraw from the study at any time. The withdrawn participants will not be replaced, and the investigator should try to contact the participants who failed to return to follow-up at the scheduled time. All data collected before withdrawal could be used for analysis. When a participant withdraws before study completion, the date and reason for withdrawal is to be documented in the eCRF and the source document, with a detailed description of the situation:

(1) Serious adverse events

(2) Adverse events (but not serious adverse events)

(3) Protocol violations

(4) Voluntary withdrawal, but not due to adverse events

(5) Going out, migrating, or moving away from the study site

(6) Loss to follow-up

---

(7) Death

(8) Other

A clear distinction must be made between subjects who withdraw from the study due to an adverse event and those who withdraw for other reasons. After withdrawal or termination of the study for the participants who have received the study vaccine, the investigator shall provide necessary treatment for the study-related clinical conditions of the participants, and follow up on the adverse events/serious adverse events until the definite diagnosis/stable disease/recovery.

Definition of withdrawal time: the time when the investigator decides to terminate the participant from the study or the time when the participant voluntarily withdraws from the study.

Definition of completion of clinical study: The clinical study is considered to be completed within 6 months after the subject completes the protective efficacy and safety visit after the booster immunization.

The study population was 18 years of age and older who had completed 2 or 3 doses of New Crown inactivated vaccine for  $\geq 6$  months.

## **8. Lost to follow-up, protocol deviation/violation, pregnancy**

### **8.1. Lost to follow-up**

When the subject can not return on time for a study visit, with full respect for the participant's rights, the investigator should make an effort to contact or recall the participant, or at least determine the participant's health status, and document the efforts made (e.g., phone call and text message logs).

---

## **8.2. Protocol deviation/protocol violation**

Protocol deviation: refers to any change and non-compliance with the clinical research protocol design or process and not approved by the Clinical Medical Research Ethics Committee. The behavior that did not affect the participant's benefits, safety, completeness, accuracy, and reliability of the study data was a mild protocol deviation. The behavior that affects the benefits, safety, and safety of the participants, or the completeness, accuracy, and reliability of the study data, is a serious protocol deviation (protocol violation)

If it is determined to be a deviation, and the deviation may affect the safety of participants, participant eligibility, or data reliability after assessment, the CRC, investigator, or designee shall report to the Clinical Research Ethics Committee and the sponsor as soon as possible; If the deviation has little or no impact on the above matters, it can be reported to the clinical medical research ethics and the sponsor after the end of the study.

Refer to the Medical Monitoring Plan and Protocol Deviation List for details.

## **8.3. Pregnancy**

The investigator shall collect the pregnancy events within 6 months after booster vaccination in female participants. Complete the Pregnancy Event Report Form within 24 hours after learning that the participant is pregnant. and report by mail to the PV department of the CRO team representing the sponsor. All pregnant women within the collection period of pregnancy events will be followed up until the end of pregnancy or 1 month after the birth of the newborn, and the records will include pregnancy outcome, delivery mode, and clinical characteristics (duration of pregnancy, outcome), birth status (gender, weight, height, newborn score) and growth and development within 1 month after birth (such as congenital anomaly or birth defect of

---

newborn shall be regarded as SAE). Pregnancy is not considered an SAE in this study, but any complication during pregnancy will be considered as an AE and in some cases can be considered as an SAE, such as spontaneous abortion, stillbirth, stillbirth, and congenital anomalies of infants. When no abnormality is found in the fetus, the induced abortion due to the mother's personal decision is not considered an adverse event. If the induced abortion event meets the SAE criteria, it is necessary to report the SAE.

## **9. Vaccines, vaccine transportation, storage and administration**

### **9.1. Investigational technology**

**Study vaccine:** SARS-CoV-2 variant mRNA vaccine (LVRNA012)

Provided by: AIM Vaccine Co., Ltd.

Dosage: 100 µg, 1.0 mL/dose

Appearance: colorless or slightly milky white liquid

Dosage form: Injection

Route of administration: intramuscular injection into the lateral deltoid muscle of the upper arm

Immunization schedule: 1 dose

Storage and transport conditions: Store and transport at -20°C±5°C.

**Control vaccine:**

Placebo: Saline

Provided by: AIM Vaccine Co., Ltd.

Dosage: 0.5mL/dose

Dosage form: Injection

Appearance: Clarified colorless liquid

Route of administration: intramuscular injection into the lateral deltoid muscle of upper arm

Immunization schedule: 1 dose

Storage and transportation conditions: Store and transport at -20°C±5°C.

---

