|                                | the vaccine.                                                                                                                                                                                                                                                                                                                                                                                                                                                                                                                                                                                                                                                                                                                                                                                                                                                                                                                                                 |
| Investigational Vaccine | 
Study vaccine: SARS-CoV-2 mRNA vaccine (LVRNA021)
 
Provided by: AIM Vaccine Co., Ltd.
 
Dosage: 100 µg /1.0 mL/dose
 
Appearance: colorless or slightly milky white liquid
 
Dosage form: Injection
 
Route of administration: intramuscular injection into the lateral deltoid muscle of the upper arm
 
Vaccination procedure: 1 dose
 
Storage and transport conditions: Should be stored and transported at -20°C ± 5°C, protected from light.
 
Placebo: Saline (0.9% sodium chloride solution)
 
Provided by: AIM Vaccine Co., Ltd.
 
Dosage: 0.5 mL/dose
 
Appearance: colorless clear liquid
 
Dosage form: Injection
 
Route of administration: intramuscular injection into the lateral deltoid muscle of the upper arm
 
Vaccination procedure: 1 dose
 
Storage and transport conditions: Should be stored and transported at room temperature.
 |

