### **6.11.2. Blinding**

An observer-blinded design will be used for this study. Before the study, the randomization statistician will provide the randomization table to the unblinded investigators who are authorized to perform vaccination-related work, and the unblinded investigators will give the injections according to the groups corresponding to the randomization numbers in the randomization table. Because the LVRNA021 vaccine and placebo are different in physical appearance, the investigators should set up blinding measures, including but not limited to syringes shading, room partitions, eye masks, etc., to prevent the participants from identifying the type of investigational vaccines based on their appearances.

The duties of drug dispensing and administration in the unblinded team must be assigned to one or more investigators who are not involved in any study of participants' evaluation. Unblinded teams and managers should avoid touching the participants as much as possible. Blind must be maintained during the generation of randomization numbers and the preparation of blind codes, the random allocation of vaccines, the vaccination of the participants, the results recording and efficacy evaluations of the investigators, the monitoring of the monitors, and data management.

Due to the inherent difference in liquid color between the study vaccine and the placebo, to ensure the feasibility of blinded design, it is necessary to appoint unblinded study staff outside the investigator's observation team for vaccination, and they are required not to disclose the participant grouping information to other relevant staff involved in the trial. To ensure that the participants are blinded, during the trial, the risk of the subjects guessing the group from the appearance of the investigational vaccine should be avoided, which may cause bias in the evaluation of safety or efficacy. Investigators who have been authorized to perform vaccination shall not be authorized to engage in tasks that may lead to unblinding such as subject blood

---

sample collection, efficacy follow-up, or safety follow-up, to ensure the blind maintenance during subject follow-up and immunogenicity blood sampling. For other specific operation instructions, please refer to the Pharmacy Manual.

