### 11.4.2. Safety observation content and indicators

Routine safety observation content includes all solicitation and non-solicitation, as well as any medical events related to or unrelated to vaccination that occur during the clinical study observation period.

Injection site (local) AE: Pain, induration, redness, rash, swelling, pruritus, cellulitis.

Non-injection site (systemic) AE: fever (axillary temperature), diarrhea, nausea, vomiting, headache, myalgia (non-injection site), arthralgia, chills, anorexia, fatigue/asthenia, acute allergic reaction

Other events: any medical event other than the above, such as acute illness, accidental injury, etc.

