#### **11.8.2.5. Safety Analysis**

---

MedDRA will be used for the medical coding of adverse events and serious adverse events, classified and counted according to the SOC and PT. The solicited adverse events for the reactogenic subgroup will be classified and counted according to the inoculation site and non-inoculation site (systemic) adverse events specified in the protocol. TEAE will be mainly analyzed in this study and the adverse events that occurred before vaccination will be listed in the form of a list. Unless otherwise specified, the following adverse events are TEAEs.

The frequency, number, and incidence of all adverse events and AESIs, adverse events and AESIs related to the study vaccine, adverse events and AESIs unrelated to the study vaccine, adverse events and AESIs of grade 3 or above, and adverse events and AESIs of grade 3 or above related to the study vaccine will be calculated respectively in the test group and control group. Fisher's precision probability test will be used to compare the differences between groups in the incidence of the above adverse events. The occurrence time and severity of adverse events will be statistically described. The adverse events and AESIs related to the study vaccine or unrelated to the study vaccine will be listed respectively.

The frequency, number, and incidence of all serious adverse events, serious adverse events related to the study vaccine, and serious adverse events not related to the study vaccine will be calculated respectively in the test group and control group. Fisher's precision probability test will be used to compare the differences between groups in the incidence of the above adverse events. The serious adverse events will be listed.

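### Vaccine is given as 1.0 mL and saline placebo as 0.5 mL, so the local-reaction contrast confounds product with a twofold volume difference

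*Protocol*

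**What the plan says.** Section 9.1 lists the study vaccine as 100 µg in 1.0 mL per dose. For the saline control it states "Dosage: 0.5mL/dose". The synopsis repeats both volumes, with "Dosage: 0.5 mL/dose" for placebo.

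Section 9.3 gives both arms the same route and site (intramuscular, lateral deltoid) and one injection each. For the control arm it says "The participants assigned to the placebo group received 1 dose of placebo on day 0". There is no top-up and no second injection.

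On blinding, section 6.11.2 describes measures "to prevent the participants from identifying the type of investigational vaccines based on their appearances" and assigns unblinded vaccinators "Due to the inherent difference in liquid color between the study vaccine and the placebo". It does not mention volume.

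On safety, section 11.4.2 solicits "Injection site (local) AE: Pain, induration, redness, rash, swelling, pruritus, cellulitis" as the local terms. Section 6.7 collects solicited events from all participants over days 0 to 14. Section 6.2.2 makes adverse-event incidence at 30 minutes, 14 days and 28 days a secondary endpoint. Section 11.8.2.5 says solicited events "will be classified and counted according to the inoculation site and non-inoculation site (systemic) adverse events specified in the protocol". For the aggregate adverse-event categories it adds that "Fisher's precision probability test will be used to compare the differences between groups in the incidence of the above adverse events".

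**The concern.** A placebo should differ from the test product only in what is being tested. Here site, route and number of injections match, but volume differs twofold and follows the arm exactly. If volume itself changes pain, swelling or induration at the injection site, the difference from saline is no longer the effect of the vaccine formulation alone.

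What is at stake is the interpretation of a secondary safety comparison. A reader will use the saline arm as the reference for how much local reaction belongs to the product, and for local events that reference is not like for like. The aggregate comparisons that include local reactions carry the same mixture, though pooling with systemic and unsolicited events could dilute it.

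A smaller point concerns blinding. The masking in section 6.11.2 is directed at appearance and colour. It would largely hide the volume from sight, but it does not address how the injection feels.

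**Working it through.** **Volumes side by side**

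| Place | Vaccine | Placebo |
|---|---|---|
| Synopsis, Investigational Vaccine | 1.0 mL | 0.5 mL |
| Section 9.1 | 1.0 mL | 0.5 mL |

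Ratio 1.0 / 0.5 = 2.0; difference 1.0 − 0.5 = 0.5 mL per injection. The two places agree, so an isolated misprint is unlikely. If 0.5 mL were nevertheless an error, staff following the document would still inject 0.5 mL.

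**Identifiability.** Each participant receives one injection: 1.0 mL of vaccine or 0.5 mL of saline. Nobody receives 1.0 mL of saline or 0.5 mL of vaccine. In any model of local reactions, the arm and volume indicators are the same variable, so only their combined effect can be estimated. Covariate adjustment and subgroup analysis cannot change that.

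**Where it enters the analysis.** Section 11.4.2 lists 7 injection-site terms and 11 systemic terms, so 7 / 18 = 39% of the listed terms are local. This is a count of terms and does not measure bias. Section 11.8.2.5 applies Fisher's test to five aggregate adverse-event categories: all, related, unrelated, grade 3 or above, and grade 3 or above and related. It names no Fisher test for injection-site events alone; those are classified and counted by arm.

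**Size.** The protocol gives no local-reaction rate and no volume effect, so the bias cannot be estimated. As a unit conversion only, each percentage point of volume effect would be 0.01 × 1,600 = 16 vaccine recipients.

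The next table is an illustration under assumed rates. It gives the probability that an excess due to volume alone would be significant at two-sided 0.05 in a direct comparison of local-reaction rates, with 1,600 per arm (normal approximation).

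| Assumed placebo rate | 1-point excess | 2-point excess | 3-point excess |
|---|---|---|---|
| 5% | 24% | 66% | 93% |
| 10% | 15% | 44% | 76% |
| 20% | 10% | 28% | 54% |

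If a volume effect of a few points exists, a trial of this size could readily detect it and it could be read as a product effect. The table is no evidence that such an effect exists.

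**The case against.** The strongest reply is that volume is part of the regimen. A recipient gets 100 µg in 1.0 mL, the local-reaction rate under that regimen is what matters for use, and the vaccine arm estimates it without bias. The protocol sets no objective of isolating formulation from volume. The protocol also does not show that volume affects local reactions. The endpoint is secondary, no safety hypothesis is tested, no named test targets local events alone, and the likely error would count against the vaccine rather than falsely reassure. A stated justification or a caveat in the report might be enough.

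Most of this stands as a limit on importance. The vaccine-arm rates are valid, the size is unknown, and efficacy is not touched. The sensation point is weak, since each participant has a single study injection with nothing to compare it against, and a Pharmacy Manual not available here may add masking detail.

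It does not remove the fault. The protocol includes a saline arm and compares adverse-event incidence between arms, so the contrast is meant to be interpreted. A caveat would disclose the confounding but leave it in place, whereas a matched volume prevents it. An error in the conservative direction is still an error in the safety contrast.

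**Conclusion.** The concern holds. The protocol consistently fixes a twofold volume difference between arms, gives no reason for it, and so makes it impossible to attribute an excess of injection-site reactions over saline to the product alone.

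The confounding is certain because it follows from the design. A non-zero volume effect, and its direction towards overstating local reactogenicity, are assumptions that the protocol does not quantify. The point is confined to the between-arm safety comparison: local events directly, and the aggregate categories with possible dilution. It is an improvement that should be made, and it does not threaten the primary analysis.

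**What to change.** Set the saline placebo to 1.0 mL per dose in the synopsis and section 9.1, and name injected volume as a matched attribute in section 6.11.2.

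Before dosing starts, the cost should be small: a different draw-up or fill volume for saline, plus edits to the protocol and the Pharmacy Manual. The protocol does not say how the placebo is filled. If numbered placebo units, including the 160 backup placebos in section 6.11.1, have already been filled at 0.5 mL, the change becomes a supply matter. If dosing has already begun, the most that can be done for those participants is to state the difference and qualify the local-reaction comparison.

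One editorial correction can go in with the same amendment. Placebo storage is given as room temperature in the synopsis, −20 ± 5 °C in section 9.1 and, as printed, 20 ± 5 °C in section 9.2. One condition should be stated throughout.
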